### **1.2 Secondary Objectives**

Secondary outcomes will examine antibiotic prescribing more broadly (including ARI diagnoses for which antibiotics might be appropriate), and extend the analysis for another 12 months of follow-up to investigate persistence of effects.

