### **4.2 Exclusion Criteria**

Visits will be excluded from the primary analysis when: 1) patients have certain medical co-morbidities that make ARI guidelines less likely to apply, 2) patients have concomitant visit diagnoses indicating a non-ARI possible bacterial infection, 3) patients have concomitant visit diagnoses indicating potentially antibiotic appropriate ARI diagnoses or other ARI diagnoses suggestive of a bacterial infection or 4) the visit occurred within 30 days of an earlier ARI diagnosis. Visits for which a provider records another condition that is not an ARI for which antibiotics might be indicated will also be excluded from the analysis. The sets of diagnoses which will be used to calculate the outcomes are listed in Appendix E: Code Set Definitions.

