### **5.3 Adherence Assessment**

In order to ensure that the study interventions are being reliably delivered we will create testing scripts that cover logical and coding variation in EHR-based interventions. Study staff will conduct site visits regularly during the intervention to ensure that tests do not fail.

Throughout the course of the study, we will also be monitoring “diagnostic drift” that may result in provider shifting diagnosis to avoid guideline conflicts that might trigger alerts or poor performance reports. Auditing programs that measure diagnostic deviation from each clinician’s 2009-2010 rates of ARI ICD-9s will trigger alerts sent to clinic coordinators if there is a statistically significant increase or decrease in the proportion of encounters coded as likely bacterial ARIs vs. likely viral ARIs. If diagnostic drift is detected, an email will be sent to the clinician indicating that the study team has observed discrepancies and that study participation requires accurate diagnoses. If three such emails are sent without evidence that a provider has corrected the pattern, s/he will be eliminated from the study.

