## 9.2 Sample Size and Randomization

Using the correction for inter-cluster correlation from Kish, we estimated the power of our study to detect a clinically significant difference between binary conditions. That is, the sample size must be inflated by a factor of  $1 + \theta(m-1)$ , where  $\theta$  is the inter class correlation and  $m$  is the number of ARI observations per cluster. In our calculations we assumed an intra-clinic correlation of 0.05 and assumed a baseline antibiotic prescribing rate of 50%, an ARI visit rate of 15 visits per month for full time providers, and independence of treatments in the factorial design. We calculated the number of visits needed for an 80% chance (1 – Type II error) to detect a clinically meaningful difference in antibiotic prescribing (7%). We assumed Type I alpha is equal to 0.05, a 75% recruitment success rate for recruiting 376 eligible providers across 49 sites, resulting in 141 providers per study factor (282 clinicians total) and a one-sided  $\alpha$  of 0.05. To achieve statistical power of 0.80 would require a total of 2,252 visits at each factor level, or 4,504 visits across all study conditions. Therefore, if each provider had a minimum of 16 antibiotic-inappropriate ARI visits over the course of the study, we would have sufficient power to detect a clinically significant effect. Randomization is described next in Section 9.2.1.

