#### 9.4.2 Secondary outcomes

To study safety and diagnostic drift we will evaluate an expanded list of potentially appropriate and other diagnoses of interest. For potentially antibiotic appropriate acute respiratory infection diagnoses these are: Acute sinusitis; Acute sinusitis/rhinosinusitis; Acute pharyngitis; 462 Acute pharyngitis. For other acute respiratory infection diagnoses or symptoms of interest these are: Streptococcal sore throat; 034.0 Acute pharyngitis; Cough; and 786.2 Acute bronchitis.

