### 9.5 Data Analyses

We will use the following descriptive statistics to characterize the sample: Means and medians for continuous measures, frequencies for count data, standard deviations and interquartile ranges for variance.

For inferential analysis of our hypotheses, we will employ a mixed-effects hierarchical logistic regression model to estimate the adjusted marginal effect over time of each intervention on the primary outcome using. Fixed effects will include intervention assignment, time period dummy variables (the baseline prescribing rate for each clinician, the intervention and intervention months 0-6, 7-12, and 13-18), and time period interacted with intervention assignment. Providers and randomization unit (clinic) will be included as random effects. To isolate the effect of each individual intervention (Suggested Alternatives, Accountable Justification, or Peer Comparison) on the primary outcome, controlling for any co-occurring interventions under the factorial design.

To assess diagnostic drift, we will use the same analytic model as for the primary outcome, but with the percentage of *all* ARIs that is coded as antibiotic-appropriate in each study arm as the dependent variable (a secondary outcome).

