**You have completed the exit survey. Thank you very much for your participation!**

## APPENDIX C: DETAILS OF DEVELOPMENT AND CUSTOMIZATION THAT WAS REQUIRED AT EACH SITE

| Requirement/Feature                                                                                                        | Longitudinal Medical Record                                                                         | NextGen                                                                                            | EpicCare                                                                                                                 |
|----------------------------------------------------------------------------------------------------------------------------|-----------------------------------------------------------------------------------------------------|----------------------------------------------------------------------------------------------------|--------------------------------------------------------------------------------------------------------------------------|
| Application of eMeasure exclusion criteria from problem list, past diagnoses, and concomitant diagnoses to suppress alerts | Not Implemented                                                                                     | Typical customization of existing functionality                                                    | Typical customization of existing functionality                                                                          |
| Justification Text Inserted into a visible portion of the medical record                                                   | Expert programming                                                                                  | Expert programming                                                                                 | Expert programming                                                                                                       |
| Default text “No justification Provided” populating medical record                                                         | Expert programming                                                                                  | Expert programming                                                                                 | Expert programming                                                                                                       |

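### The primary denominator depends on diagnoses entered after randomisation by clinicians who know their assignment, so selective recoding of treated visits biases the estimate towards benefit; the planned checks detect this only in part

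*Protocol*

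**What the plan says.** The primary outcome (Section 9.4.1, Table 1) is the antibiotic rate at visits coded with a non-antibiotic-appropriate ARI. Section 4.2, repeated under Outcome measures in Section 9.1, removes a visit when there is a concomitant code for a possible non-ARI bacterial infection, when "patients have concomitant visit diagnoses indicating potentially antibiotic appropriate ARI diagnoses or other ARI diagnoses suggestive of a bacterial infection", and, in a closing sentence, when another non-ARI condition that could justify an antibiotic is recorded. Section 4.3 has the educational module tell clinicians which interventions their site received.

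The protocol is alert to recoding. Section 5.3 names "provider shifting diagnosis to avoid guideline conflicts that might trigger alerts or poor performance reports" as a risk. It audits each clinician's ARI coding against 2009-2010 rates, alerts clinic coordinators, emails the clinician, and removes a provider after three emails without correction. Section 9.5 adds a drift analysis with the primary model, in which the share of all ARIs that "is coded as antibiotic-appropriate in each study arm as the dependent variable" is a secondary outcome.

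On a wider outcome, Section 1.2 states: "Secondary outcomes will examine antibiotic prescribing more broadly (including ARI diagnoses for which antibiotics might be appropriate"; Section 3 says much the same. Section 9.4.2 gives the expanded list another purpose: "To study safety and diagnostic drift we will evaluate an expanded list of potentially appropriate and other diagnoses of interest". Section 9.5 describes inference for the primary outcome and the drift share only.

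**The concern.** The analysed visits are chosen by a variable that the interventions can change. The codes are recorded after randomisation, and a visit with an antibiotic has more reason to be recoded than one without. Table 1 shows that Peer Comparison is scored on the primary-outcome codes. Appendix C lists "Application of eMeasure exclusion criteria from problem list, past diagnoses, and concomitant diagnoses to suppress alerts" as a feature built into NextGen and EpicCare, so at those sites an added exclusion code can also silence the alert. The difference-in-differences model in Section 9.1 cancels coding habits that stay constant over time; it does not cancel a change in coding caused by the intervention. Selective recoding therefore biases the primary comparison towards the interventions, and a fall in the coded rate could be read as a fall in antibiotic use.

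**Working it through.** **Inputs (Section 9.2).** The protocol "assumed a baseline antibiotic prescribing rate of 50" percent and a planned difference of 7%. I take this as 7 percentage points, 50% to 43%; the text does not say absolute or relative. The provider arithmetic reproduces: 376 x 0.75 = 282, 141 per factor level, and 2,252/141 = 16.0 visits each. The 2,252 is used below for scale only.

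**Step 1: size of the artefact.** Let a fraction f of treated visits leave the denominator, with no untreated or control visit recoded and no antibiotic avoided. The measured rate is (0.5 - 0.5f)/(1 - 0.5f).

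| Treated visits leaving (f) | Share of all visits | Measured rate | Apparent fall (points) |
|---|---|---|---|
| 5% | 2.5% | 0.475/0.975 = 48.7% | 1.3 |
| 10% | 5% | 0.45/0.95 = 47.4% | 2.6 |
| 15% | 7.5% | 0.425/0.925 = 45.9% | 4.1 |
| 20% | 10% | 0.40/0.90 = 44.4% | 5.6 |
| 25% | 12.5% | 0.375/0.875 = 42.9% | 7.1 |

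**Step 2: what the full 7 points needs.** The share x of all visits solves (0.5 - x)/(1 - x) = 0.43, so x = 0.07/0.57 = 12.3%, which is 12.3/50 = 24.6% of treated visits. On 2,252 visits, 1,126 are treated; removing 277 leaves 849/1,975 = 43.0%, with all 1,126 antibiotics still written. That is about 2 of each provider's 16 visits. If the 7% were relative (50% to 46.5%), x = 0.035/0.535 = 6.5%, or 13.1% of treated visits.

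**Step 3: sensitivity of the 24.6%.**
- Baseline of 30%, 40% or 60%, from 0.07/(1 - (p - 0.07)) divided by p: 30.3%, 26.1% or 24.8%.
- Control clinics also recode 5% or 10% of treated visits: 28.4% or 32.3% is needed.
- 5% or 10% of untreated visits are recoded too, from 1 - (0.43/0.57)(1 - u): 28.3% or 32.1%.

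**Step 4: would the Section 9.5 drift share show it?** The document gives no baseline share s of ARIs coded antibiotic-appropriate; I assume 20%, 30% or 40%, counting only primary and antibiotic-appropriate codes.
- Visits move to an antibiotic-appropriate ARI code. The rise is (1 - s)x. For the 7-point artefact (x = 0.123) it is 9.8, 8.6 or 7.4 points. At 10% of treated visits (x = 0.05) it is 4.0, 3.5 or 3.0.
- A non-ARI infection code is added. If Section 9.5 still counts the visit as an ARI, the share does not move. If the visit is dropped, the new share is s/(s + (1 - s)(1 - x)). The rise is 2.2, 2.8 or 3.2 points for the 7-point artefact, and 0.8, 1.1 or 1.2 at 10%.

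The Section 5.3 audit likewise compares bacterial-type with viral-type ARI coding, so an added non-ARI code is not its target.

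**The case against.** The protocol does more than note the risk. The individual audit, coordinator alerts, emails and possible removal form an active deterrent, and Section 10.3.2 has a committee review coding dashboards before each email distribution. A large shift into sinusitis or pharyngitis should show in the drift outcome. The incentive is also weaker than it first looks. Table 1 shows that sinusitis, pharyngitis, streptococcal sore throat and cough still trigger decision support, so moving a visit there does not escape the alerts. The Appendix A module tells Peer Comparison clinicians that their sinusitis and pharyngitis rates will be reported too. Appendix C records exclusion-based suppression as not implemented in the Longitudinal Medical Record, although there the clinician indicates whether the antibiotic is for an ARI. The broader outcome is promised, its extra codes sit in a separate file (Appendix E), and modelling detail for secondary outcomes is commonly left to a SAP.

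All of that stands as a limit on size and likelihood. It does not protect the primary estimate: deterring or detecting drift does not correct the denominator, and removing a provider is a further post-randomisation exclusion beside the intent-to-treat statement in Section 9.1. Nor do Sections 9.4.2 and 9.5 match the purpose that Sections 1.2 and 3 give the broader outcome.

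Three stronger readings are not supported. A reader might infer that recoding is likely to produce the whole planned effect; the documents give no recoding rate, and that case needs about one treated visit in four with no recoding elsewhere. A reader might infer that the drift measure is blind to non-ARI codes; Section 9.5 does not say whether the exclusions apply to its denominator, so zero is one reading only. A reader might infer that no broader prescribing outcome is planned; Sections 1.2 and 3 say one is.

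**Conclusion.** The point holds as a bias that can occur and runs towards benefit, not as one shown to be large. At the plan's 50% rate, selective recoding of 5% to 10% of treated visits gives 1.3 to 2.6 points of apparent effect against a planned 7. The full 7 needs about 25%, or 28% to 32% if untreated or control visits are also recoded at 5% to 10%. These figures assume that recoding falls on treated visits and that no antibiotic is avoided; the recoding rates are illustrative. The existing checks would probably reveal a large move into antibiotic-appropriate ARI codes. They respond little or not at all to added non-ARI codes, and the protocol does not say how the primary result is read if drift differs by arm. Label: cheap improvement.

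**What to change.** Keep the primary outcome. In Sections 9.4.2 and 9.5:

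1. Specify the broader outcome of Section 1.2 as the same mixed model for any antibiotic at all otherwise eligible visits with any Table 1 ARI code, without the visit-diagnosis exclusions (items 2 and 3 of Section 4.2 and its closing sentence on other conditions). Report it beside the primary result as a sensitivity analysis.
2. Model, by intervention, the visit-level indicator that an ARI visit was removed by a visit-diagnosis exclusion, counting non-ARI codes.
3. State that, if removal or drift differs by arm, the primary result is described as a change in the coded rate and interpreted together with the all-ARI estimate and its confidence interval. A rule asking only that the two estimates point the same way would be poor: a null effect would pass about half the time, and a diluted true effect could fail by chance.

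The cost is wording and two further runs of the same model on data already extracted. The downside is that the all-ARI effect is diluted and less precise: if half of the visits were in the primary class, 7 points there would be 7 x 0.5 = 3.5 overall. It also includes visits where an antibiotic may be appropriate, and it still misses a visit whose ARI code is replaced outright by a non-ARI code.

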### **4.3 Study Enrollment Procedures**

All clinicians with adult patients in participating practices will be contacted by email and in-person meetings. Enrollment and consent will be conducted using an online survey administration application.

The email includes a description of the broad goals of the study, a general description of the intervention, compensation providers would receive for participation, and a link to the electronic consent form and baseline survey.

The baseline survey includes an educational module. After providing consent, providers are asked to complete a 15 to 20 minute online survey and educational module. The educational module contains information about ARIs derived from evidence based guidelines and systematic reviews. The educational module also describes the interventions to which a clinician's site was assigned,

including changes they would observe in their EHR (for Accountable Justifications and Suggested Alternatives interventions) and examples of the kinds of emails they would receive (Peer Comparison). These examples include Appendix B: Example of Suggested Alternatives Order Set and Appendix C: Sample Peer Comparison Email Text.

## **5. STUDY INTERVENTIONS**

### **5.1 Interventions, Administration, and Duration**

The intervention period will be 18-months in length for all participants, with a one year follow-up period to measure persistence of effects after interventions end. The pre-intervention baseline period will be 6 months in length.

### **5.2 Handling of Study Interventions**

The following interventions will be compared: *Accountable Justification (AJ)* is an EHR-based intervention that will prompt the clinician to justify, in a free text response, the decision to prescribe an antibiotic for each ARI. The prompt is designed to inform the clinician that the justification will be seen by others in the patient's medical record as an "Antibiotic Justification" note, and that if no justification is entered, the phrase "no justification given" will appear in the note. *Suggested Alternatives (SA)* is an EHR-based intervention most closely resembling traditional clinical decision support alerts and order sets. ARI diagnoses will trigger a pop-up screen that states, "Antibiotics are not generally indicated for [this diagnosis]. Please consider the following prescriptions, treatments, and materials to help your patient." The screen will then suggest a list of alternatives see Appendix D: Example of Suggested Alternatives order set), each with a streamlined order entry option, such as for over-the-counter and prescription medications (e.g., decongestants) and letter templates excusing patients from work. *Peer Comparison (PC)* is an email-based intervention. Clinicians will be ranked from highest to lowest inappropriate prescribing rate within each region using EHR data. Clinicians with the lowest inappropriate prescribing rates (the top-performing 10th percentile) will be informed that they are a "Top Performer" in a congratulatory email. The remaining clinicians will be told that they are "Not a Top Performer" by email. Emails will include the number and proportion of inappropriate antibiotic prescriptions written for a month for non-antibiotic-appropriate ARI cases and the proportion written by Top Performers.

### **5.3 Adherence Assessment**

In order to ensure that the study interventions are being reliably delivered we will create testing scripts that cover logical and coding variation in EHR-based interventions. Study staff will conduct site visits regularly during the intervention to ensure that tests do not fail.

Throughout the course of the study, we will also be monitoring “diagnostic drift” that may result in provider shifting diagnosis to avoid guideline conflicts that might trigger alerts or poor performance reports. Auditing programs that measure diagnostic deviation from each clinician’s 2009-2010 rates of ARI ICD-9s will trigger alerts sent to clinic coordinators if there is a statistically significant increase or decrease in the proportion of encounters coded as likely bacterial ARIs vs. likely viral ARIs. If diagnostic drift is detected, an email will be sent to the clinician indicating that the study team has observed discrepancies and that study participation requires accurate diagnoses. If three such emails are sent without evidence that a provider has corrected the pattern, s/he will be eliminated from the study.

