## **9. STATISTICAL CONSIDERATIONS**

### **9.1 General Design Issues**

#### *Hypotheses*

Our primary hypothesis is that practices randomized to receive behavioral economic interventions will have decreases over time in antibiotic prescribing rates for non-antibiotic appropriate ARIs, compared to contemporaneous antibiotic prescribing rates for non-antibiotic appropriate ARIs among control practices. This hypothesis will be evaluated in an intent-to-treat difference-in-differences framework using a mixed-effects logistic regression model. Fixed effects will include the effects of interventions over time (i.e., interactions between randomization assignment and time), using a 6-months prior to the intervention baseline period. Providers and randomization unit (clinic) will be modeled as random effects.

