#### *Outcome measures*

The primary outcome measure is the rate of antibiotic prescribing for non-antibiotic-appropriate acute respiratory infections.

The ICD-9 codes for primary outcomes are defined in detail in Sections 9.4.1 and 9.4.2 of

this protocol document. These outcomes are computable clinical quality measures from the electronic health record. These are widely used in medicine to evaluate quality improvement and reliability and validity are generally supported. As a secondary outcome, effects on potentially appropriate acute respiratory infection diagnosis will be evaluated with respect to diagnostic drift and safety (see Section 9.4.2).

An office visit is eligible for inclusion in the outcome denominator if: 1) the patient was 18 years old or older, 2) the provider and practice site were enrolled in the study, 3) the visit occurred during the 18-month intervention period, and 4) the patient did not have a visit with any ARI diagnosis in the prior 30 days. Visits are excluded from the primary analysis when: 1) patients have certain medical co-morbidities that make ARI guidelines less likely to apply, 2) patients had concomitant visit diagnoses indicating a non-ARI possible bacterial infection, or 3) patients had concomitant visit diagnoses indicating potentially antibiotic appropriate ARI diagnoses or other ARI diagnoses suggestive of a bacterial infection. Visits for which a provider recorded another condition that was not an ARI for which antibiotics might be indicated were also excluded from the analysis.

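### Eliminating clinicians for uncorrected diagnostic drift after randomisation conflicts with the intent-to-treat analysis and weakens the drift outcome

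*Protocol*

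**What the plan says.** Four parts of the protocol bear on this.

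- **Section 5.3 (Adherence Assessment).** The drift paragraph begins "Throughout the course of the study, we will also be monitoring" and gives the reason for concern as "provider shifting diagnosis to avoid guideline conflicts that might trigger alerts or poor performance reports". The audit compares each clinician with his or her own 2009-2010 coding and is triggered by a "statistically significant increase or decrease in the proportion of encounters coded as likely bacterial ARIs vs. likely viral ARIs". The last step is: "If three such emails are sent without evidence that a provider has corrected the pattern, s/he will be eliminated from the study".
- **Section 9.1 (Hypotheses).** "This hypothesis will be evaluated in an intent-to-treat difference-in-differences framework using a mixed-effects logistic regression model".
- **Sections 4.1 and 9.1 (Outcome measures).** A visit enters the denominator only if, among other conditions, "the provider and practice site were enrolled in the study".
- **Section 9.5.** "To assess diagnostic drift, we will use the same analytic model as for the primary outcome", with the share of all ARIs coded antibiotic-appropriate as the dependent variable. Drift is thus a secondary outcome compared between arms.

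No section says what happens in the analysis to the visits of an eliminated clinician, before or after elimination.

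**The concern.** Elimination is a post-randomisation event that depends on how the clinician reacts. Section 5.3 itself ties the reaction to alerts and poor performance reports, and these are the randomised interventions. If eliminated clinicians' visits leave the data, the comparison is no longer between clinics as randomised, and the loss can differ between arms.

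Two results are exposed. The primary contrast could be biased by selective loss of clinicians. The drift outcome would lose the clinicians it exists to detect, and a finding of no drift is what a reader needs in order to trust the primary result.

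**Working it through.** The protocol gives no figure for elimination, so the main check sets the passages side by side. The arithmetic after it is illustration on assumed values.

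**1. The text**

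| Question | Protocol | Consequence |
|---|---|---|
| When does elimination occur? | 5.3: throughout the study; 6.1: randomisation on Day 1, interventions from Month 1 | It can occur after randomisation |
| What triggers it? | 5.3: a persistent change in bacterial versus viral coding | It can be a response to assignment |
| Who is covered? | 5.3: every clinician, either direction of change | It can occur in all arms, including control |
| Which visits count? | 4.1 and 9.1: visits to enrolled providers | Loss of visits is the likelier reading of elimination |
| Which principle governs? | 9.1: intent-to-treat | Dropping those visits contradicts it |

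**2. Primary contrast**

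From Section 9.2: a 50% baseline rate and a 7-point target difference. Assumed: non-drifting intervention clinicians fall by 7 points, drifters and controls do not truly change, clinicians have equal visit numbers, and drifters make up a share f of the intervention clinicians.

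- All visits kept: effect = 7 × (1 − f)
- Drifters dropped: effect = 7
- Overstatement = 7 × f

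| f | Kept | Dropped | Overstatement (points) |
|---|---|---|---|
| 5% | 6.65 | 7.0 | 0.35 |
| 10% | 6.30 | 7.0 | 0.70 |
| 20% | 5.60 | 7.0 | 1.40 |

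The largest value is one fifth of the target (1.4/7).

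The sign is not secure. The table counts drifters at their true, unchanged rate. A 50% prescriber who recodes half of the antibiotic visits out of the denominator is recorded at 0.25/0.75 = 33.3%, an apparent fall of 16.7 points. Dropping that clinician makes the arm's recorded fall smaller, not larger.

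**3. Drift outcome**

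Assume drifters raise the share coded antibiotic-appropriate by d points and other clinicians by none. The effect with everyone kept is f × d.

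- Smallest case: 0.05 × 10 = 0.5 points
- Largest case: 0.20 × 30 = 6 points
- All drifters' visits deleted: 0

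If visits are only censored from elimination onwards, the visits that led to the emails remain. Section 9.5 estimates effects by period (months 0-6, 7-12 and 13-18), so earlier periods would still show drift and later ones would tend towards none.

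**4. Why the drift outcome matters**

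Let x be the share of visits that were given an antibiotic and are recoded out of the denominator, with no change in prescribing. The recorded rate falls from 50% to 43% when (0.50 − x)/(1 − x) = 0.43, so x = 0.07/0.57 = 12.3% of visits. That is about a quarter of the antibiotic visits (0.123/0.50). This is the harm done by drift itself. It does not measure the effect of elimination.

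**The case against.** The strongest reply is that elimination is not defined. The sentence sits in an adherence section, enrolment is dated at consent (Section 6.2.2), a clinician eliminated later was still enrolled, and Section 9.1 says intent-to-treat. Elimination could therefore mean only that participation ends while the records are kept, and a statistical analysis plan, not available here, may say so. This stands in part: loss of visits is the likelier reading but not a certain one. The protocol nevertheless states both the rule and the principle without reconciling them. If elimination stops data capture, no later plan can restore the visits.

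The rule also has a sound purpose. As step 4 shows, unchecked recoding could imitate the whole target effect, and retaining drifters leaves that recoding in the primary outcome.

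Three stronger readings are tempting, and the documents do not support them.

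- **A reader might infer that removing high prescribers simply lowers an arm's rate.** For example, removing a tenth of clinicians at an assumed 70% gives (0.50 − 0.10 × 0.70)/0.90 = 47.8%. That is a shift in level. The primary analysis is a difference-in-differences with provider effects, which largely absorbs a stable high rate.
- **A reader might infer that repeated testing would eliminate many clinicians by chance.** The protocol gives neither a significance level nor an audit schedule, and it requires three emails without correction, not any three flags. With assumed independent 5% tests at 18 monthly audits, the chance of three flags in a row is 0.05³ × (1 + 15 × 0.95) = 0.19%, or about 0.5 of 282 clinicians.
- **A reader might infer that control clinicians have no reason to drift.** All clinicians receive the educational module and know they are being studied, and changes in either direction count.

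**Conclusion.** The conflict is real and should be fixed. Section 5.3 states a post-randomisation elimination that depends on behaviour linked to the interventions, Section 9.1 promises intent-to-treat, and nothing in the protocol retains the visits. The conclusion rests on reading elimination, together with the enrolled-provider condition, as dropping some or all visits.

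The direction and size of the primary bias are unknown. The 0.35 to 1.4 points hold only under the assumptions in step 2. The effect on the drift outcome is clearer in direction: removal tends to hide drift, fully if all of a clinician's visits are deleted and partly if they are censored. How many clinicians would be eliminated cannot be derived from the protocol, and the contradiction does not depend on that number.

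**What to change.** - **Section 5.3:** state that elimination ends study contact only.
- **Section 9.5:** state that all eligible visits of clinicians enrolled at randomised clinics, before and after elimination, stay in the primary and drift analyses under the randomised clinic assignment.
- **Reporting:** give drift emails and eliminations by arm. Confine any analysis that excludes eliminated clinicians to a sensitivity analysis.
- **Check on recoding:** present the broader ARI antibiotic outcome already planned in Section 1.2 beside the primary outcome, because it is less sensitive to recoding.

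The cost is about two sentences plus a small table by arm. Records already arrive weekly (Sections 3 and 10.2), and consent already covers their inclusion in the study database (Section 6.2.1). The downside is that recoding by retained drifters stays in the primary outcome; the drift and broader ARI outcomes are there to reveal it.
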